#### Exclusion criteria

Distant metastasis at enrollment;Prior or planned total laryngectomy;Moderate/severe dysphagia at enrollment per baseline videofluoroscopy DIGEST grade ≥ 2 (as graded per central laboratory review),Previously seen by speech language pathologist for swallowing therapy for the current head and neck cancerDiagnosis of second primary non-head and neck cancers in the thorax or the central nervous system at enrollmentHead and neck radiotherapy for thyroid or cutaneous/skin primary tumors, regardless of neck fields.

There will be no purposeful exclusion by age within adult age (18 years of age and older), sex, gender, race, or ethnicity. Instead, the composition of age, women, and minorities will reflect the demographic of subjects with HNC who are treated at participating sites. We will adhere to NIH standards for maintaining and presenting data on self-declared race and ethnicity including two ethnic categories (Hispanic/Latino and Non-Hispanic or Latino) and five racial categories (American Indian or Alaska Native, Asian, Black or African American, Native Hawaiian or other Pacific Islander, and White).

At each participating site, coordinators will screen tumour board lists and radiation treatment schedules weekly to identify potentially eligible patients. Site coordinators will then approach the patient at or after their next standard of care clinic appointment (e.g., with radiation oncology, medical oncology, surgery, or speech language pathology) to obtain consent, after a member of the treatment team has first discussed the trial with the patient. All eligible patients who provide informed consent will be consecutively enrolled to capture a representative spectrum of the target population. A screening log will detail clinicopathologic and demographics of all patients screened, approached, enrolled and randomized to examine the representative nature of the trial, and will be transparently reported in accordance with Consolidated Standards of Reporting Trials (CONSORT) standards [30, 31].

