### Screening before randomization

After giving written informed consent, participants fulfilling all eligibility criteria will be enrolled in the study. Participants will only be randomly assigned to the study intervention after screening for no/mild baseline dysphagia using videofluoroscopic swallow (VFS) study digital recordings. The screening step requires independent and blinded central laboratory review of the baseline VFS by trained speech language pathologists. Baseline dysphagia is operationally defined as a DIGEST [32] grade of > 2. Screen failure information will be captured in the electronic database to ensure transparent reporting according to the CONSORT guidance. The minimal data set in the screening log includes demography (age, sex, tumor and treatment plan), screen failure details, and eligibility criteria.

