The PSS-HN [54] is a 3-item validated semi-structured interview tool capturing normalcy of diet, public eating, and, understandability of speech. Each item is scored from 0 to 100, with the higher score indicating better performance. The PSS-HN correlated well with the FACT-HN, especially for normalcy of diet and eating in public (r = 0.66, *p* < 0.0001; r = 0.42, p < 0.0001, respectively) and is a reliable tool, sensitive to differences in functioning when applied to HNC patients [55]. The PRO-ACTIVE trial adaptation of PSS-HN includes additional questions regarding tracheotomy status and feeding tube utilization.
5)Medical Outcome of Dysphagia (MOD)

The Medical Outcomes of Dysphagia (MOD) is a newly developed 3-part inventory that targets patient reported symptoms related to health consequences secondary to dysphagia, namely: malnutrition (MOD-Nutrition), aspiration pneumonia (MOD-Pulmonary) and mood changes such as depression and anxiety (MOD-Psychology) [56]. The MOD-Nutrition sub-scale consists of 13 items, of which all but one have either a 3, 4 or 5-point ordinal response; the remaining item quantifies food intake. The MOD-Pulmonary sub-scale consists of 11 items, of which all have a 5-point ordinal response. Likewise, the MOD-Psychology sub-scale consists of 45 items, of which all have a 5-point ordinal response. The study assessing reliability and divergent validity of the items in the three MOD subscales has recently been completed, and included over 350 patients, among whom 77% had a diagnosis of dysphagia secondary to head and neck cancer. Each of the sub-scales has excellent inter-rater reliability with the following total score ICC (95% confidence interval): MOD-Nutrition, ICC = 0.84 (0.73–0.91); MOD-Pulmonary, ICC = 0.89 (0.81–0.94); and, MOD-Psychology ICC = 0.90 (0.83–0.94). The items on the MOD were derived from an extensive review of the literature combined with collective opinion of clinicians, patients and caregivers [56].
6)Cancer Behavior Inventory – Version 3 (CBI-V3)

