### Statistical analysis

#### Primary endpoint

For the primary endpoint, an intention-to-treat (ITT) approach will be applied incorporating a gate-keeper method to control risk of Type 1 error in the setting of multiple comparisons [64, 65]. The primary hypothesis (Hyp 1.1) is that the combined PRO-ACTIVE interventions (PRO-ACTIVE EAT and PRO-ACTIVE EAT+EXERCISE) will result in a better swallow outcome compared to RE-ACTIVE as measured by duration of feeding tube use in the first year after the completion of RT. If PRO-ACTIVE is superior in Hyp 1.1, we will assess the dose response of the PRO-ACTIVE arms. The secondary hypothesis (Hyp 1.2) is that the most intensive intervention (PRO-ACTIVE EAT+EXERCISE) will be more effective than the least intensive (PRO-ACTIVE EAT).

The initial analysis will compare the RE-ACTIVE group to the combined PRO-ACTIVE groups in terms of the duration of feeding tube use operationalized as count of days of tube use from end of RT to last tube use within the 12-month study period by means of a multiple linear regression model with covariate adjustment. The presence of a feeding tube which is not being used for feeds is disregarded. The treatment effect will be expressed as absolute mean difference along with 95% confidence intervals. If this test yields *p* < 0.05, the two PRO-ACTIVE groups (EAT versus EAT+EXERCISE) will be compared using the same linear analysis method. The meaningful variables we will include in the regression model are: age (as a continuous variable); HPV status (oropharyngeal site vs all others); surgery (yes/no); chemotherapy (yes/no); radiation dose (as a continuous variable); and, facility (as a categorical variable to account for practice variation across the eleven sites).

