#### Secondary endpoints

The analysis of the secondary endpoints is not dependent on the findings of the primary endpoint. The hypothesis (Hyp 2.1) is that the combined PRO-ACTIVE interventions will result in a better secondary outcomes including videofluoroscopic swallowing evaluations, functional status measures, health status measures, and patient reported outcomes 3 months following the completion of RT. For the secondary outcomes, ITT analysis will again use a gate-keeper approach to assess differences between arms. Continuous outcomes will be evaluated with ANCOVA approach (multiple linear models regressing outcome on randomization arm plus the baseline measure for adjustment) at the 3-month post-treatment interval when a baseline measurement is present and a t-test (or suitable replacement) otherwise. The treatment effect will be expressed as the mean adjusted difference, or equivalently, mean adjusted change along with 95% confidence intervals. Binary outcomes will be compared by means of a chi-square test or Fisher’s exact test if expected counts are less than 5 and treatment effects will be expressed as risk differences with 95% confidence intervals. Sensitivity will be assessed in terms of consistency of inference as well as magnitudes of effect size using distributional measures of Minimal Clinically Important Difference (MCID) [67] or anchor-based MCID [44] when available to interpret whether observed differences are meaningful. Exploratory analyses will be conducted on all outcomes with repeated measurements using mixed-effect models to examine time by treatment interactions. Exploratory subgroup analyses will examine the relative benefit or harm of the PRO-ACTIVE and RE-ACTIVE swallowing interventions in relevant subgroups according to the following: patient (age, tumor site, prior surgery); and provider (radiation dose, chemotherapy use, prophylactic feeding tube use).

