### Sample size calculation

Sample size calculations, based on a 2-sample t-test, assume 952 patients enrolled with 1:4 allocation to RE-ACTIVE (Arm 1, *n* = 190) and PRO-ACTIVE arms (Arms 2 and 3, *n* = 381 per group). The attrition factor is set at 5% because the primary endpoint can be ascertained without clinical encounter. Thus, the resultant sample size estimated is 180 in Arm 1, 361 in Arm 2, and 361 in Arm 3. For the primary comparison (Hyp 1.1) of Arm 1 (*n* = 180) versus the combined Arms 2 and 3 (*n* = 722), assuming ITT analysis with type 1 error probability of 0.05 (two-sided) yields 80% power to detect a small effect size of .23 SD for duration of feeding tube use. For the analysis of Hyp 1.2 in the gate-keeper approach, we will compare intensity of PRO-ACTIVE therapies (Arm 2 versus Arm 3, *n* = 361 per group), assuming type 1 error probability of 0.05 (two-sided), we have 80% power to detect again a small effect size of 0.21 SD for the primary endpoint of feeding tube duration. We expect the t-test will not be sufficient as the primary analysis given it does not allow for covariate adjustment. Therefore, we will apply the multiple linear regression model as the primary analysis for Aim 1. The power calculation conducted assuming t-tests for analysis of hypotheses 1.1 and 1.2 and deriving a sample of 952 patients remain sufficient for the linear model because by adjusting for variables associated with the mean response, the distribution of the residuals is expected to improve. Therefore, the power for the same hypothesized difference in the primary outcome attributed to treatment in the regression framework will be at least as much as for that for the t-test.

For the secondary analysis (Aim 2) in the gate-keeper approach, we will compare intensity of PRO-ACTIVE therapies (Arm 2 versus Arm 3, *n* = 361 per group), assuming type 1 error probability of 0.05 (two-sided), we have 80% power to detect again a small effect size of 0.24 SD for PROs and VFS measures. The attrition factor for the secondary analysis is set at 26% because they are more prone to attrition due to required clinical visits and survey responses required from participants. As an exception, feeding tube dependence at 3-months uses an attrition factor of 5%, for the same rationale as the primary endpoint.

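### The primary model could also adjust for baseline swallowing and diet, which the trial already collects: a low-priority efficiency gain, not an error

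*Protocol article*

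**What the plan says.** **Primary model.** In the protocol article, Statistical analysis, Primary endpoint, tube days are compared by multiple linear regression. "The meaningful variables we will include in the regression model are" introduces six items: age, HPV status (oropharyngeal site against all others), surgery, chemotherapy, radiation dose and facility. It reads as a closed list. The same method is used for Hyp 1.1 (RE-ACTIVE against the combined PRO-ACTIVE arms) and Hyp 1.2 (EAT against EAT+EXERCISE).

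**Baseline swallowing data.** Screening before randomization states: "Participants will only be randomly assigned to the study intervention after screening for no/mild baseline dysphagia". It adds: "The screening step requires independent and blinded central laboratory review of the baseline VFS by trained speech language pathologists". Exclusion criteria rule out "Moderate/severe dysphagia at enrollment per baseline videofluoroscopy DIGEST grade ≥ 2 (as graded per central laboratory review". Table 1 schedules PSS-HN and MDADI at baseline. Secondary outcomes describes PSS-HN as a "3-item validated semi-structured interview tool capturing normalcy of diet, public eating, and, understandability of speech", each item scored 0 to 100.

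**Adjustment elsewhere.** Continuous secondary outcomes that have a baseline value are analysed with "multiple linear models regressing outcome on randomization arm plus the baseline measure for adjustment". Sample size calculation expects the regression to have at least the power of the t-test because "by adjusting for variables associated with the mean response, the distribution of the residuals is expected to improve".

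**The concern.** The endpoint is presented as a swallowing outcome, and patients enter with either no or mild dysphagia. Swallowing and diet at entry are natural candidate predictors of later tube use, and both are recorded as part of the trial. Leaving them out may make the confidence interval slightly wider than it need be. It also leaves a chance difference in mild dysphagia between arms unadjusted: randomisation is stratified by site only, and RE-ACTIVE has about 180 evaluable patients.

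Power for Hyp 1.1 has no margin, and Hyp 1.2 is tested only if Hyp 1.1 succeeds, so a small gain on the first comparison helps both. Adding such terms after an imbalance has been seen would be post hoc, so the choice belongs in the pre-specified list.

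**Working it through.** **Inputs from Sample size calculation.** Two-sided alpha 0.05; 180 against 722 evaluable patients at 0.23 SD (Hyp 1.1); 361 against 361 at 0.21 SD (Hyp 1.2); 80% power stated for each.

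**Step 1. Reproduce the stated power** (normal approximation): SE = √(1/n₁ + 1/n₂), power = Φ(d/SE − 1.96).

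- Hyp 1.1: SE = √(1/180 + 1/722) = 0.0833 SD; 0.23/0.0833 = 2.761; Φ(0.801) = 78.8%. Detectable effect at 80% power = (1.960 + 0.842) × 0.0833 = 0.233 SD.
- Hyp 1.2: SE = √(2/361) = 0.0744 SD; 0.21/0.0744 = 2.821; Φ(0.861) = 80.5%. Detectable effect 0.209 SD.

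The detectable effects round to the stated 0.23 and 0.21, with no credit taken for any covariate.

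**Step 2. Add baseline terms.** If they explain a share R² of the variance left after the listed covariates, the SE is multiplied by √(1 − R²), and effective evaluable N is 902/(1 − R²). The article gives no R², so the values below are assumptions.

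| Assumed R² | SE multiplier | Power, Hyp 1.1 | Power, Hyp 1.2 | Detectable effect, Hyp 1.1 | Effective N |
|---|---|---|---|---|---|
| 0 (as planned) | 1.000 | 78.8% | 80.5% | 0.233 SD | 902 |
| 1% | 0.995 | 79.2% | 80.9% | 0.232 SD | 911 |
| 2% | 0.990 | 79.6% | 81.3% | 0.231 SD | 920 |
| 5% | 0.975 | 80.9% | 82.5% | 0.227 SD | 949 |

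For 1% to 5%, the gain for Hyp 1.1 is 0.4 to about 2 points, worth roughly 9 to 47 evaluable patients.

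**Step 3. DIGEST alone.** With grade 2 and above excluded, only grades 0 and 1 remain. If a share q has grade 1 and the grades differ by d within-grade SDs in tube days, R² = q(1−q)d² / [1 + q(1−q)d²]. Both q and d are assumed.

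- d = 0.25: R² = 0.010 at q = 0.2 and 0.015 at q = 0.5. The Hyp 1.1 gain is under 1 point.
- d = 0.5: R² = 0.038 at q = 0.2 and 0.059 at q = 0.5. The gain is about 1.5 to 2.4 points.

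This ignores any overlap with the six listed covariates, so it errs on the generous side. The entry rule does not directly truncate PSS-HN diet, which might add more, but the article gives no figure.

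**Step 4. Chance imbalance.** Assume 40% have mild dysphagia. The SD of the difference in that share between 190 and 762 randomised patients is √[0.24 × (1/190 + 1/762)] = 0.040, or 4 points. A 2-SD imbalance (8 points), with an assumed 0.4 SD longer tube use in mild patients, shifts the estimate by 0.08 × 0.4 = 0.032 SD. That is 14% of 0.23 SD and 0.38 of one standard error.

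**The case against.** The strongest reply is that nothing here is wrong. A linear model with six pre-specified covariates is a valid analysis, and the sub-group section cites preliminary data linking five of them (age, HPV status, surgery, dose, chemotherapy) to swallowing outcomes. That stands. A reader might infer more, in four ways that the article does not support:

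- **That the comparison is biased or the error rate inflated.** Randomisation protects both. Chance imbalance of the size in Step 4 is already within what the confidence interval allows for.
- **That the plan contradicts its own secondary analyses.** Those models adjust each outcome for its own baseline value and use a t-test or suitable replacement where none exists. Days of tube use counted from the end of radiotherapy have no pre-treatment value, so there is no conflict.
- **That the power argument fails.** It claims only power at least equal to the t-test, and the t-test figure reproduces without covariates.
- **That precision is known to be lost.** The reported r = −0.49 relates DIGEST to diet in survivors, not pre-treatment grade to later tube days. It comes from a sample not limited by this trial's entry rule, and restricting the grade to 0 or 1 usually weakens a correlation.

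The reply is also right that the change is not entirely free. Only DIGEST is a condition of randomisation. PSS-HN is an interview, and a note to Table 1 provides for its being missed in clinic. A complete-case fit could drop patients and cancel a gain of one or two points.

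**Conclusion.** The point holds as a modest, low-priority efficiency improvement. The list contains no measure of swallowing or diet at entry, although DIGEST is available for every correctly randomised patient and PSS-HN is scheduled. The planned analysis is valid and its power of about 80% is correctly stated.

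The gain rests entirely on an assumed prognostic strength beyond the six covariates. At 1% to 5% of residual variance it is 0.4 to about 2 points of power for Hyp 1.1 and 0.4 to 2 points for Hyp 1.2. If the measures add nothing, the gain is nil. Adjustment for chance imbalance in mild dysphagia is a further small benefit. The facts about what is collected and what is listed are certain; the size of the gain is not.

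**What to change.** Before unblinding, add two terms to the pre-specified covariates for Hyp 1.1 and Hyp 1.2: baseline DIGEST grade (categorical) and baseline PSS-HN normalcy of diet (continuous). State that a missing baseline PSS-HN is handled by simple imputation or a missing indicator, so that no randomised patient is dropped for a missing covariate.

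Reconcile the DIGEST cut-offs. Exclusion criteria use a grade of 2 or more, whereas Screening before randomization defines baseline dysphagia as a grade above 2. The reconciled rule determines which levels the covariate can take.

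The cost is a wording change and a few degrees of freedom out of about 900. No new data are needed.

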#### Secondary endpoints

The analysis of the secondary endpoints is not dependent on the findings of the primary endpoint. The hypothesis (Hyp 2.1) is that the combined PRO-ACTIVE interventions will result in a better secondary outcomes including videofluoroscopic swallowing evaluations, functional status measures, health status measures, and patient reported outcomes 3 months following the completion of RT. For the secondary outcomes, ITT analysis will again use a gate-keeper approach to assess differences between arms. Continuous outcomes will be evaluated with ANCOVA approach (multiple linear models regressing outcome on randomization arm plus the baseline measure for adjustment) at the 3-month post-treatment interval when a baseline measurement is present and a t-test (or suitable replacement) otherwise. The treatment effect will be expressed as the mean adjusted difference, or equivalently, mean adjusted change along with 95% confidence intervals. Binary outcomes will be compared by means of a chi-square test or Fisher’s exact test if expected counts are less than 5 and treatment effects will be expressed as risk differences with 95% confidence intervals. Sensitivity will be assessed in terms of consistency of inference as well as magnitudes of effect size using distributional measures of Minimal Clinically Important Difference (MCID) [67] or anchor-based MCID [44] when available to interpret whether observed differences are meaningful. Exploratory analyses will be conducted on all outcomes with repeated measurements using mixed-effect models to examine time by treatment interactions. Exploratory subgroup analyses will examine the relative benefit or harm of the PRO-ACTIVE and RE-ACTIVE swallowing interventions in relevant subgroups according to the following: patient (age, tumor site, prior surgery); and provider (radiation dose, chemotherapy use, prophylactic feeding tube use).

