## Aims and hypotheses

To address this evidence gap, the primary aim (Aim 1) of the PRO-ACTIVE trial is to compare the effectiveness of PRO-ACTIVE versus RE-ACTIVE swallowing interventions among patients with HNC planned to undergo RT. We hypothesize that at 12-months post radiotherapy the combined PRO-ACTIVE therapies are more effective than RE-ACTIVE therapy (Hyp 1.1); and, if so, that more intensive PRO-ACTIVE (EAT + EXERCISE) is superior to less intensive PRO-ACTIVE (EAT) (Hyp 1.2). Effectiveness will be measured based on reduced duration of feeding tube dependency, a pragmatic outcome valued by diverse stakeholders including patients, caregivers and clinicians [13, 21, 25, 26].

The second aim (Aim 2) of the PRO-ACTIVE trial is to compare the relative benefit or harm of PRO-ACTIVE to RE-ACTIVE swallowing intervention on all secondary outcomes at both 3- and 12- months post radiotherapy, namely: swallowing impairment, maximum interincisal opening (trismus), swallowing-related QOL, symptom burden, self-reported pneumonia, malnutrition and mood disorder, cancer coping strategies, diet level, feeding tube rates, weight loss, hospitalization and/or emergency department (ED) presentation. In addition, the second aim will compare the benefit on reduced duration of feeding tube presence at 3-month post radiotherapy. Our hypothesis for this second aim is that the combined PRO-ACTIVE interventions will result in better secondary outcomes at 3- and 12- months following the completion of RT (Hyp 2.1). As in our primary aim, for each secondary outcome for which PRO-ACTIVE is superior, dose response of the PRO-ACTIVE arms will be examined hypothesizing the more intensive therapy as superior (Hyp 2.2).

The third aim (Aim 3) of the PRO-ACTIVE trial is to explore the relative benefit or harm of the PRO-ACTIVE and RE-ACTIVE swallowing interventions in relevant subgroups according to the following: age, tumor site, prior surgery, radiation dose, chemotherapy use, and prophylactic feeding tube use. Our hypothesis for this third aim is that all interventions will be more effective in the following higher risk subgroups: older age; non-HPV related cancer sites; prior surgery; higher radiation dose; chemotherapy (yes); and, prophylactic feeding tube insertion (yes).

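### The Aim 2 gate-keeper works only within each secondary outcome, so superiority claims over 13 or more outcomes carry no type 1 error control across them

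*Protocol article*

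**What the plan says.** Under Aims and hypotheses, Aim 2 is a directional hypothesis: "combined PRO-ACTIVE interventions will result in better secondary outcomes at 3- and 12- months following the completion of RT (Hyp 2.1"). The outcomes begin with "swallowing impairment, maximum interincisal opening (trismus), swallowing-related QOL, symptom burden, self-reported pneumonia, malnutrition and mood disorder" (seven) and continue with coping, diet level, feeding tube rates, weight loss, and hospital or emergency visits (five). Feeding tube duration at 3 months is added separately. The second step, Hyp 2.2, is described as follows: "for each secondary outcome for which PRO-ACTIVE is superior, dose response of the PRO-ACTIVE arms will be examined hypothesizing the more intensive therapy as superior".

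Under Secondary endpoints, the link to the primary result is removed: "The analysis of the secondary endpoints is not dependent on the findings of the primary endpoint". The next rule is: "For the secondary outcomes, ITT analysis will again use a gate-keeper approach to assess differences between arms". That section restates Hyp 2.1 for one time point only, ending with "patient reported outcomes 3 months following the completion of RT".

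Under Primary endpoint, the gate-keeper is introduced as a device against type 1 error when several comparisons are made. There it orders two tests on one outcome.

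Under Sample size calculation, the Aim 2 statement is for Arm 2 versus Arm 3: two-sided 0.05 with "80% power to detect again a small effect size of 0.24 SD for PROs and VFS measures".

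The word exploratory is used for the mixed models and the subgroup analyses. It is not used for Hyp 2.1 or Hyp 2.2.

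**The concern.** A gate-keeper that orders two tests on a single outcome controls error for that outcome. When the same two-step scheme is repeated separately on each of many outcomes, every outcome gets its own fresh first test. The condition "for each secondary outcome for which PRO-ACTIVE is superior, dose response of the PRO-ACTIVE arms will be examined" makes clear that the scheme runs outcome by outcome.

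Taken with the sentence that frees the secondary outcomes from the primary result, the stated rules permit the following. Hyp 1.1 fails, one of 13 or more secondary outcomes reaches p < 0.05 by chance, PRO-ACTIVE is called superior on it, and an intensity effect is then tested on that same outcome. Because the word again ties this scheme to the one used for error control on the primary endpoint, a reader may credit Aim 2 with protection that it does not have. The trial is meant to settle best practice and guide resource allocation, so an isolated secondary claim could carry weight.

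**Working it through.** **1. The plan's own Aim 2 figure.** 381 per arm less 26% attrition is 381 × 0.74 = 281.9. The detectable difference at two-sided 0.05 and 80% power is (1.960 + 0.842) × √(2/281.9) = 0.236 SD, and power at 0.24 SD is 81%. The printed 0.24 SD is therefore reproduced at an unadjusted 0.05. (The 361 per group printed beside it would give 0.209 SD; that is a separate point.) The figure is for Hyp 2.2. The article states no alpha or power for Hyp 2.1.

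**2. Inputs.**
- Number of Hyp 2.1 tests at 3 months: 12 listed outcomes + 3-month tube duration = 13. This counts one test per listed outcome; testing several subscales would add more.
- Number if 12 months is also tested formally: 12 × 2 + 1 = 25. Aims and hypotheses implies this; Secondary endpoints does not.
- Level per test: two-sided 0.05, inferred from the repeated gate-keeper method (p < 0.05 on the primary) and the 95% confidence intervals.
- Correlation between test statistics: not given, so assumed from 0 to 0.7.

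**3. Chance of at least one false rejection of Hyp 2.1 under the global null.**
Independent tests, either direction: 1 − 0.95^13 = 48.7% and 1 − 0.95^25 = 72.3%. Independent tests, only in favour of PRO-ACTIVE: 1 − 0.975^13 = 28% and 1 − 0.975^25 = 46.9%. Correlated tests: simulation of equicorrelated normal statistics, 200,000 draws per setting.

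| Correlation | 13 tests, either direction | 13 tests, favouring PRO-ACTIVE | 25 tests, either direction | 25 tests, favouring PRO-ACTIVE |
|---|---|---|---|---|
| 0 | 49% | 28% | 72% | 47% |
| 0.3 | 42% | 22% | 61% | 32% |
| 0.5 | 34% | 17% | 47% | 23% |
| 0.7 | 24% | 12% | 32% | 16% |

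The per-test reference is 5% in either direction, or 2.5% in favour of PRO-ACTIVE.

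**4. What the within-outcome gate-keeper changes.** Under the global null it changes nothing in the table, because Hyp 2.2 is tested only after Hyp 2.1 has been rejected and the first false claim has already been made. If PRO-ACTIVE truly helps on many outcomes, the Hyp 2.2 tests on those outcomes all open. They then form a second family, of up to the same size, with no control across outcomes.

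**The case against.** The strongest objection is that rules for multiplicity across secondary outcomes are usually left to the statistical analysis plan, which is not shown, and that a journal article condenses. This stands as far as it goes: the absence of a ranking or an alpha split is not itself the point, and nothing here shows that the analysis plan lacks one. However, the article does fix two rules, independence from the primary result and a gate-keeper that runs per outcome. An analysis plan would have to qualify both.

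Several stronger readings are tempting but not supported:
- A reader might infer that the plan promises 5% over the secondary outcomes and misses it. The article ties error control to the primary endpoint and sets no familywise level for Aim 2.
- A reader might quote a single error rate, such as 34% or 47%. Those values need a correlation of 0.5, which the article does not give, and they count false results against PRO-ACTIVE as well as for it.
- A reader might take 0.05 as stated for every secondary test. It is stated only for Arm 2 versus Arm 3.
- A reader might take 25 tests as settled. Only the 3-month tests are supported in both sections.
- A reader might conclude that secondary testing must depend on Hyp 1.1. Aim 2 covers harms as well as benefits, so that is a debatable trade-off and not a correction of an error.

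The article also plans effect estimates, 95% confidence intervals and interpretation against minimal clinically important differences. That helps the reader judge size, but it does not control type 1 error.

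**Conclusion.** The point holds in this form. Aim 2 is written as superiority hypotheses on 12 outcomes plus 3-month tube duration, detached from the primary result, and the stated gate-keeper gives no control across outcomes or time points. With 13 tests at an inferred two-sided 0.05, the chance of at least one false rejection under the global null is about 24% to 49% for assumed correlations of 0.7 to 0, and about 12% to 28% for false claims favouring PRO-ACTIVE. If 12 months is also tested formally, the ranges are about 32% to 72% and 16% to 47%. The exact size depends on these assumptions. The lack of control across outcomes follows from the stated rules alone. The primary analysis is not affected.

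**What to change.** In Secondary endpoints, state two things. First, the within-outcome gate-keeper does not control type 1 error across the secondary outcomes. Second, Aim 2 results are supportive or exploratory, reported as estimates with 95% confidence intervals and without a confirmatory superiority claim, in particular when Hyp 1.1 is not significant. Also state whether Hyp 2.1 is tested at 3 months only or at 3 and 12 months, since the two sections differ.

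If the sponsor wants confirmatory secondary claims, it should name a short list of key secondary outcomes and time points of its own choice. It should then apply Holm or a fixed testing order across them at two-sided 0.05, with Hyp 2.2 following within an outcome.

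The cost is wording only: no new patients or data. The downside is that an isolated secondary p < 0.05 can no longer be claimed as confirmatory. All estimates, including those on harms, are still reported.
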